***Intervention***: The intervention consists of a nurse-led self-help based on Preventive Cognitive Therapy (PCT). Patients are offered a detailed treatment manual of the therapy with literature, backgrounds and assignments, and have weekly telephone contact with a nurse. The therapy consists of eight sessions with a fixed structure. Patients in the control condition receive care as usual.

***Main study parameters/endpoints*:** Primary outcome is the cumulative rate of recurrences of depression meeting DSM-IV criteria, assessed with the Structured Clinical Interview for DSM-IV at baseline and at 3,6,9,12 and 15 months follow-up. For the economic evaluation, quality of life is measured using the EuroQol and 12-item Short Form Health Survey (SF-12). Costs are measured from a societal perspective using the TIC-P. Moderator analyses are conducted for demographic characteristics, number of previous depressive episodes, age of onset of first depression, self-efficacy in preventing depression, satisfaction with PCT, pain and fatigue in order to indentify subgroups that show particularly good response to the intervention.

***Nature and extent of the burden and risks associated with participation, benefit and group relatedness*:** Benefits regarding participation in this trial are the effective preventive cognitive therapy that is offered to patients in a new setting and a regular check for depressive symptoms. Burden associated with participation are the questionnaires that patients must fill in at 3,6,9,12 and 15 months follow-up and the time to complete the assignments of the self-help (approximately 1,5 hours a week). Risks in this trial are very low because usual care, including the use of AD, is permitted in both arms.

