Several risk factors for recurrent depression have been defined 17 including premature anti-depressant withdrawal, socio-demographic factors such as age and gender, longer duration of individual episodes and poor symptom control during continuation therapy. Younger age of onset of first depressive episode, low socioeconomic status, low self-efficacy for managing depression and symptoms of pain and/or fatigue also act as risk factors for recurrent depression.

Besides, several subgroup analyses, based on stratified 18,19 and non-stratified 15 subsamples, suggest that PCT is more effective in ‘high risk’ patients meaning patients with a history of at least three episodes on a life time basis. Recall-bias often hampers assessment of the number of previous episodes on a life-time basis. Therefore it is better to select patients on the number of episodes during a shorter time frame of say, 2 episodes in the last five years.

Only few studies have focused on psychological interventions aimed at the prevention of recurrences in primary care patients with depression 20.

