# 2. OBJECTIVES

**Primary Objective:**

To study whether nurse-led self-help is (cost-) effective for persons with recurrent MDD in primary care in comparison with usual care. Effectiveness is defined as significantly less SCID/DSM-V recurrences of MDD in one year follow-up compared to usual care. Cost-effectiveness is evaluated from a societal perspective meaning that the costs of the intervention, other health care utilization, patients' out-of-pocket costs and costs due to productivity losses will be included in the economic evaluation.

It is hypothesized that adding nurse-led self-help to usual care is clinically superior to care as usual alone for preventing recurrence in recurrent depressive disorder. In addition, it is expected that the intervention dominates the comparator condition in terms of (cost-) effectiveness.

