**Secondary Objective(s):**

To study whether nurse-led self-help for patients with recurrent MDD versus usual care alone:

A) reduces health care utilisation

B) is effective in reducing co-morbid distress, anxiety and somatisation

C) is satisfying according to patients

D) is (cost)-effective in certain subgroups of patients, particularly related to (i.e. modified by):

- the number of previous episodes

- type of treatment for the last recurrence (AD, psychological intervention, nothing etc).

- the severity of residual depressive symptoms in the remitted phase

- age of onset of the first depressive episode,

- social economic status (education)

- self-efficacy for managing depression

- symptoms of pain and/or fatigue

- long duration of individual episodes

- socio-demographic factors such as age and gender

- pattern use of antidepressants

The secondary objectives lead to the hypotheses below about effect modification.

*RE: Reduction in health care utilisation*

The substantial economic burden of depression is partly due to an increased health care utilisation. Evidence shows that health care costs of depressed patients are higher compared with matched controls even after adjusting for co-morbidity30. This is not only true for mental but also for general medical care utilization. Therefore, it is hypothesized that by preventing recurrences through this intervention, health care utilisation and related costs in these patients will also be reduced.

*RE: B (cost-) effective in reducing co-morbid levels of psychopathology*

Psychiatric comorbidity in depression is associated with greater symptom severity, severer functional impairments and a more chronic course of the disease. Comorbid psychopathology in depressed patients is common and often involves anxiety and somatisation.

Anxiety consists of irrational and diffuse fears and avoidance behaviour. Somatisation consists of a range of psychosomatic symptoms like headache, muscle pains, cardiovascular and gastrointestinal symptoms31. It is hypothesized that with the reduction of (risk for) recurrences, the co-morbid level of anxiety and/or somatisation will also decrease.

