# 3. STUDY DESIGN

This study is a randomised controlled trial with randomisation at patient level. There will be two parallel groups to evaluate the costs and effects of nurse-led self-help + usual care for 134 primary care patients with remitted MDD versus 134 controls (usual care) at 3, 6, 9 and 12 months follow up. Stratification variables will be the number of previous episodes (cut-off point at 4 or more previous episodes in the last 5 years) and the type of treatment as usual received for the last episode (psychological intervention / AD / no care).

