**9.4 Analysis of secondary clinical outcomes**

Moderator analyses will be conducted for some demographic variables. Subgroups that show particularly good response to the intervention will be identified by regressing HRDS depression severity on the interaction term of treatment and clinical characteristics of the patients as measured at baseline. Examples of other characteristics are number of previous depressive episodes, treatment preference, age of onset of first depression, self-efficacy in preventing depression, pain and fatigue, social economic status other demographic characteristics like gender, marital and occupational status and age.

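### The clinical moderator model in section 9.4 uses HRSD severity, so effect modification on recurrence has no planned analysis, and the Summary adds a moderator (satisfaction) whose treatment interaction cannot be estimated

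*Protocol*

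**What the plan says.** Section 2 (Primary Objective) fixes what effective means: "Effectiveness is defined as significantly less SCID/DSM-V recurrences of MDD in one year follow-up compared to usual care". SCID recurrence is also the primary outcome in sections 7.1.1 and 9.2.

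Secondary objective D asks whether the intervention "is (cost)-effective in certain subgroups of patients, particularly related to (i.e. modified by" a list of patient characteristics. The explanatory text for D in section 2 argues largely from recurrence risk. For pain and fatigue it names the outcome as the cumulative incidence of depression, together with health care costs.

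Section 9.4 gives the clinical moderator analysis: "Subgroups that show particularly good response to the intervention will be identified by regressing HRDS depression severity on the interaction term of treatment" and characteristics measured at baseline. No other outcome is named there. Section 7.1 does not list the HRSD among the primary or secondary endpoints, although Table 1 schedules it from T0 to T5.

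Section 9.5 adds an incremental net benefit regression with the same predictors for the cost-effectiveness side.

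The Summary gives its own moderator list, which includes "self-efficacy in preventing depression, satisfaction with PCT, pain and fatigue in order to indentify subgroups". Sections 7.1.2 and 7.3 restrict the satisfaction questionnaire (CSQ-8) to the 15-month visit and to 40 intervention patients: the 20 with the best and the 20 with the worst course in terms of recurrence.

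**The concern.** A moderator analysis is useful when it says for whom the main effect is larger or smaller. Here the main effect is on recurrence and the moderator model is on symptom severity. The two can disagree. Under section 9.2 a recurrence counts if it is present at the assessment or has occurred since the last one, whereas a severity score taken at a visit need not register an episode that has already resolved. A subgroup found on HRSD might not be one in which recurrence is prevented, and the reverse is equally possible. Readers would nevertheless take the subgroup results as a statement about the effectiveness that section 2 defines.

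Satisfaction is a separate problem. A moderator in a treatment-interaction model must be defined in both arms and should not be a consequence of treatment. Satisfaction with PCT meets neither condition.

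**Working it through.** **Outcome, set side by side**

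| Place in protocol | Outcome |
|---|---|
| Section 2, definition of effectiveness | SCID recurrence |
| Sections 7.1.1 and 9.2, primary outcome | SCID recurrence, Poisson model |
| Section 2, objective D | (Cost-)effectiveness by subgroup |
| Section 9.4, clinical moderators | HRSD severity |
| Section 9.5, economic moderators | Net benefit (effect times willingness to pay, minus cost) |

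No row tests whether the treatment effect on recurrence differs by baseline characteristic. Section 9.5 does not fill the gap. Net benefit combines effect and cost, and the effect unit in the cost-effectiveness analysis of section 9.3 is depression-free person years.

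**Satisfaction, set side by side**

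- The Summary lists it as a moderator.
- Section 9.4 restricts moderators to baseline characteristics and does not list it. Objective D does not list it either. In section 2 it belongs to objective C.
- Table 1 shows the CSQ-8 at T5 only. Sections 7.1.2 and 7.3 limit it to 20 + 20 = 40 intervention patients.
- With no control-arm values, the treatment by satisfaction term cannot be separated from the satisfaction term. Choosing the 40 by their recurrence outcome also distorts the within-arm association.

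**What moving to recurrence would cost in power (illustration)**

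Section 4.4 gives no recurrence rates, so I first looked for rates that reproduce its 107 per arm (two-sided alpha 0.05, power 0.80, absolute difference 0.20). With 0.60 against 0.40:

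- Uncorrected: n = [1.960 × √(2 × 0.5 × 0.5) + 0.842 × √(0.24 + 0.24)]² / 0.20² = 96.9, or 97.
- Continuity-corrected: n = (96.9/4) × [1 + √(1 + 4/(96.9 × 0.20))]² = 106.7, or 107.

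The stated figure is thus reproduced with 0.60 against 0.40, which motivates an assumed control rate of 0.60.

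For the interaction I assume 0.60 control recurrence in both subgroups, a high-risk share s of 20 to 50%, and work on the risk-difference scale. The contrast is d = RD(high) − RD(low). Its variance is the sum of p(1 − p)/n over the four cells, and power is approximately Φ(d/SE − 1.96).

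Example with 134 per arm, s = 0.5 (67 per cell), RD 0.30 against 0.10:

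- SE = √[(0.21 + 0.24 + 0.25 + 0.24)/67] = √0.01403 = 0.118.
- d/SE = 0.20/0.118 = 1.69, so power = Φ(−0.27) = 0.39.

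| Risk differences (high, low) | 107 per arm | 134 per arm |
|---|---|---|
| 0.30, 0.10 | 23 to 33% | 28 to 39% |
| 0.40, 0.00 | 73 to 88% | 82 to 94% |

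The two sizes are the analysable number in section 4.4 and the arm size in the Summary and section 3. The Poisson model works on the ratio scale, so these figures show the order of magnitude only.

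**The case against.** The best defence of section 9.4 is power. A continuous score is usually more sensitive than a binary outcome for interaction tests, and the table above shows that recurrence interactions of moderate size would often be missed. That stands. It is a reason to keep HRSD as a supportive outcome and to call the analyses exploratory, but not to leave out the outcome by which the protocol defines effectiveness.

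The visit at which HRSD enters the model is not named, but a statistical analysis plan commonly settles that, so I do not count it as a fault.

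Satisfaction appears as a moderator only in the Summary. In section 2 it serves objective C, as an association among patients who received this format, and the 40-patient sample was designed for that. This is correct, and it makes the item a local contradiction that one deletion cures.

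Two stronger readings are tempting, and the protocol supports neither:

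- A reader might infer that objective D as a whole is unanswered. It is not, because section 9.5 addresses its cost-effectiveness half. Nor are all the subgroup hypotheses about recurrence alone: residual symptoms are linked to cost-effectiveness, pain partly to health care costs, and education to treatment response.
- A reader might infer that the analysis splits prior episodes at the wrong point, because the stratification uses a "cut-off point at 4 or more previous episodes in the last 5 years" while section 1.1 reports more benefit in "patients with a history of at least three episodes on a life time basis". But the cut at 4 is a randomisation stratum. Section 2 says stratification allows the factor to be studied as a modifier, but section 9.4 names the number of episodes without any cut. The counts also cover different windows, five years against a lifetime. Any estimate of a diluted subgroup contrast would need an analysis split that the protocol does not prescribe and a share of three-episode patients that it does not give.

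**Conclusion.** The point holds in two parts. First, the clinical moderator model is fixed on HRSD severity, so effect modification on recurrence, the clinical half of objective D, has no planned analysis. Second, the Summary names a moderator whose interaction with treatment cannot be estimated and which conflicts with the baseline rule in section 9.4.

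Both follow from the text alone and need no numerical assumption. The consequence is confined to secondary analyses: the primary estimate, its test and the economic moderator analysis are unaffected. The change should be made, but the trial does not depend on it. The power figures rest on the assumed 60% control recurrence, subgroup shares and risk differences. They describe the cost of the remedy and do not measure the defect.

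**What to change.** 1. In section 9.4, make the main clinical moderator analysis a set of treatment by baseline-characteristic interaction terms added to the Poisson recurrence model of section 9.2. Keep the HRSD model as supportive.
2. Label the moderator analyses exploratory.
3. In the Summary, delete satisfaction with PCT from the moderator list. It remains under objective C as a description within the intervention arm.

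This costs wording only. The SCID, the HRSD and the baseline measures are already scheduled, and neither the sample nor the visits change. The downside is lower interaction power on a binary outcome, so a null interaction on recurrence should be reported with its confidence interval and not read as evidence of a uniform effect.

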**9.5 Analyses of secondary economic outcomes**

Analogous to the moderator analyses for clinical end-terms, an incremental net benefit regression (INBR) analysis will be conducted to addresses the research question in what groups the intervention is likely to be particularly cost-effective. The same set of predictor variables (see above) will also be used in these INBR analyses.

The Incremental Net Benefit will be calculated as Eλ –C. The first term is the number of units of effectiveness gained multiplied by an unknown quantity (λ) what one is willing to pay (WTP) for a unit of effectiveness gained. Because λ is unknown, we will use a likely WTP-range. The product term is subtracted by the costs yielding the net benefit expressed in monetary terms. Incremental net-benefits will be obtained using a regression analysis approach and these help to identify moderators (sub-groups) for which the intervention is particularly cost-effective53.

## 9.6 Interim analysis (not applicable)

An interim analysis can be performed during a running clinical trial for reason of safety and efficacy. The main reason for interim analysis on efficacy is to verify whether important clinical differences exist between the treatment group and the control group have become evident. The main reason for interim analysis on safety are performed to guarantee the safety of the patients during the trial. Because efficacy is best to be expected only after 12 months of follow-up and safety-issues are hardly to be expected in this non-medicine trial, an interim analysis will not be performed. Any possible issues with blinding and privacy are prevented this way.

#

# 10. ETHICAL CONSIDERATIONS

## 10.1 Regulation statement

This study will be conducted according to the principles of the Declaration of Helsinki

(Version 2004) and with the Medical Research Involving Human Subjects Act (WMO). By

signing this protocol the investigators commit themselves to conduct this study in according

to Good Clinical Practice (GCP).

## 10.2 Recruitment and consent

Only when a patient fulfils both inclusion- and exclusion criteria, the subject will be included.

## 10.3 Objection by minors or incapacitated subjects (if applicable)

*N/A*

## 10.4 Benefits and risks assessment, group relatedness

Risks in this trial are very low because usual care is permitted in both arms. Regarding benefits; PCT has proven effective in preventing recurrences in patients with MDD. Besides, the authors of this protocol have good experiences with offering PCT in patients with MDD. This study should be performed in this specific group of patients with a history of recurrences because the effect of the prevention therapy is highest in this high-risk group.

## 10.5 Compensation for injury

The sponsor/investigator has a liability insurance which is in accordance with article 7, subsection 6 of the WMO.

The sponsor (also) has an insurance which is in accordance with the legal requirements in the Netherlands (Article 7 WMO and the Measure regarding Compulsory Insurance for Clinical Research in Humans of 23rd June 2003). This insurance provides cover for damage to research subjects through injury or death caused by the study.

1. € 450.000,-- (i.e. four hundred and fifty thousand Euro) for death or injury for each subject who participates in the Research;
2. € 3.500.000,-- (i.e. three million five hundred thousand Euro) for death or injury for all subjects who participate in the Research;
3. € 5.000.000,-- (i.e. five million Euro) for the total damage incurred by the organisation for all damage disclosed by scientific research for the Sponsor as ‘verrichter’ in the meaning of said Act in each year of insurance coverage.

The insurance applies to the damage that becomes apparent during the study or within 4 years after the end of the study.

## 10.6 Incentives (if applicable)

N/A

# 11.ADMINISTRATIVE ASPECTS AND PUBLICATION

## 11.1 Handling and storage of data and documents

Data are collected in digital patient record forms. The construction and maintenance of this

electronic Case Report Form (eCRF) is handled by the department of data management of

the VU Medical Centre/ EMGO. The department of data management will build and manage a database based on these eCRF’s. Study data are handled confidentially and anonymously

and in accordance with the Dutch personal data protection act (de wet bescherming

persoonsgegevens). Subjects have unique identification codes (study number). Study

related data that are not directly linked to clinical patient management are stored using that

study number.

## 11.2 Amendments

Amendments are changes made to the research after a favourable opinion by the accredited METC has been given. All amendments will be notified to the METC that gave a favourable opinion. Non-substantial amendments will not be notified to the accredited METC and the competent authority, but will be recorded and filed by the sponsor.

## 11.3 Annual progress report

The sponsor/investigator will submit a summary of the progress of the trial to the accredited METC once a year. Information will be provided on the date of inclusion of the first subject, numbers of subjects included and numbers of subjects that have completed the trial, serious adverse events/ serious adverse reactions, other problems, and amendments.

## 11.4 End of study report

The investigator will notify the accredited METC of the end of the study within a period of 8 weeks. The end of the study is defined as the last patient’s last visit.

In case the study is ended prematurely, the investigator will notify the accredited METC, including the reasons for the premature termination.

 Within one year after the end of the study, the investigator/sponsor will submit a final study report with the results of the study, including any publications/abstracts of the study, to the accredited METC.

